### Outcome measures

#### Procedure of assessments

The control group will receive all questionnaires by mail. The intervention group will receive the questionnaires at baseline and at 18-week follow-up, also by mail; the questionnaires at post-treatment will be handed out together with a short group evaluation questionnaire in the last group session. For returning the questionnaires, participants will be provided with stamped and addressed envelopes. The session questionnaires for the process evaluation of the group program will be handed out after each session, and patients will be asked to complete and return them immediately after the group session.

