## Methods/Design

### Study design

This is a randomized, wait-list controlled trial. Study participants allocated at random to the intervention group will participate in the CBT group program for patients with somatic diseases and depressive or adjustment disorders immediately after contacting the clinic. Study participants allocated at random to the wait-list control group will follow the usual waiting process of our outpatient clinic. After completion of the follow-up assessment (about five months after randomization), study participants of the wait-list control group are also offered to participate in the group program. The three measurement points are scheduled for all study participants at baseline (immediately before initial consultation, T_1_), 10 weeks after randomization (post-treatment, T_2_) and 18 weeks after randomization (follow-up, T_3_). The 18-week follow-up measurement is scheduled in a relatively short interval of two months after treatment because we did not want to extend the usual waiting period of four months for individual psychotherapy for patients in the wait-list control group. For an overview of the study design see Fig. 1.

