#### Intervention design

The STEpS group program consists of eight weekly sessions of 100 minutes. The group size will be limited to eight patients and the group setting will be half-open: entry for new members will be possible with every new topic (every other session). The group program will be performed by a psychotherapist trained in CBT with experience in group psychotherapy. Before joining the group, new group members will have a short consultation with the group therapist for about 20 minutes. This consultation serves to get to know each other, to reduce any fears, to clarify any questions and to inform the new patient about the topics and procedures of the group program and the group rules (for example listening to each other and letting the other person finish talking). Patients will also receive a folder with an overview of the group topics, the group rules and enough space for their work sheets and individual notes. Furthermore, all patients will give their written consent that they will treat all information provided by other group members confidentially. The group sessions will take place at the outpatient clinic of the Institute for Psychology at the Albert-Ludwigs-University of Freiburg. During the sessions, tea and water will be offered and a short break of 10 minutes will be included.

The STEpS group program covers the following topics: behavioral activation (two sessions), cognitive restructuring (two sessions), coping with illness, social support, self-esteem and meaning. Every session will start with an exercise of progressive muscle relaxation as described by Jacobson [40], and with everybody giving a short summary of his or her current situation. Mindfulness-based exercises (for example, leaves on a stream) will be used as a break or closing exercise, but will not be a regular feature of the group program. All sessions will end with a final round (‘How do you feel at this moment? What is your personal take home message?’). For a detailed session overview see Table 1.

**Table 1 Tab1:** Overview of the STEpS group program

Session	Topic	Content
1	Behavioral activation I	- Psycho-education about the relationship between behavior and emotion: explanation of the downward mood spiral [60]
		- Selection of individual positive activities from a checklist [61] and rating of the selected activities
		- Scheduling three positive activities for the next week
2	Behavioral activation II	- Review of homework

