#### Outcome measures

Table 2 shows an overview of all variables and measurements.

**Table 2 Tab2:** Key variables and measurements

Variables	Measurement	T_1_	Monitoring	T_2_	T_3_
Inclusion and exclusion criteria					
Psychiatric disorders (Axis-I)	SCID-I	x	-	-	-
Somatic disorders	self-report in telephone screening	x	-	-	-
Primary outcomes					
Anxiety and depressive symptoms	HADS-D	x	-	x	x
Secondary outcomes					
Psychological distress	BSI	x	-	x	x
Current psychosocial distress	NCCN Distress Thermometer	x	-	x	x
Changes in experience and behavior since baseline	VEV-VW	-	-	x	x
Health-related quality of life	SF-12	x	-	x	x
State of self-esteem	SSES-revised	x	-	x	x
Subjective need for psychotherapy	newly developed questions	x	-	x	x
Process evaluation					
Acceptance of treatment	treatment attendance, self-report	-	x	-	-
Therapeutic processes during the group program from patients’ perspectives	BPSR-G 2000	-	x	-	-
Covariates					
Demographic variables (sex, age, family status, education, employment, and so forth)	demographic survey	x	-	-	-
Psycho-pharmacotherapy	demographic survey	x	-	-	-
Pretreatment of psychiatric disorders	demographic survey	x	-	-	-
Psychological treatment since baseline	self-report	-	-	x	x
Changes in somatic health and psycho-pharmacotherapy since baseline	self-report	-	-	x	x
Coping with a chronic disease	TSK	x	-	-	-

*T*
_*1*_ baseline/pretreatment, *T*
_*2*_ post-treatment/10 weeks after randomization, *T*
_*3*_ follow-up/18 weeks after randomization, *BPSR-G-2000* Bern Post Session Report 2000 modified for groups, *BSI* Brief Symptom Inventory, *HADS*-*D* Hospital Anxiety and Depression Scale, German version, *SCID*-*I* Structured Clinical Interview for DSM-IV Axis I Disorders, *SF*-*12* Short Form Health Survey, *SSES*-*revised* State Self-Esteem Scale, revised version, *TSK* Trier Scales of Coping with Disease, *VEV*-*VW* revised short form of Change Questionnaire of Experience and Behavior

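### At T2 the outcome questionnaires are tied to the last group session in the intervention arm but mailed to controls, which risks uneven timing and attendance-related missing data in one arm

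*Protocol article*

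**What the plan says.** Under Procedure of assessments, the two arms are handled differently at one time point only. For controls, "The control group will receive all questionnaires by mail". The intervention arm gets baseline and the 18-week follow-up by post, but "the questionnaires at post-treatment will be handed out together with a short group evaluation questionnaire in the last group session". On return of the forms, no arm is singled out: "For returning the questionnaires, participants will be provided with stamped and addressed envelopes". Completion on the spot is requested only for the session process questionnaires, where "patients will be asked to complete and return them immediately after the group session".

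Under Study design, T2 is a calendar point for both arms: "The three measurement points are scheduled for all study participants at baseline", at 10 weeks and at 18 weeks after randomization. The footnote to Table 2 treats the end of treatment and week 10 as the same moment: "post-treatment/10 weeks after randomization".

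Under Intervention design, the programme has eight weekly sessions, a cap of eight patients, and entry only at every second session. Statistical analyses promises an intention-to-treat comparison of the main outcomes at T2 and T3, with missing data probably imputed by a method valid under missing at random.

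**The concern.** T2 has two anchors. For controls it is a number of weeks since randomization. For intervention patients it is a session, whose date depends on when they joined the group. Where the two disagree, the arms are measured at different times on a scale (HADS-D) that asks about the last week only.

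In addition, receipt of the form depends on attendance in one arm and on nothing but a postal address in the other. Followed as written, an intervention patient who never starts, drops out or misses the last session is not reached by the stated T2 route. The plan itself expects some dropout from the group, because it uses dropout to measure acceptance. If non-attendance goes with poorer outcome, T2 scores would be missing selectively in the intervention arm, and the intention-to-treat comparison at T2 would be weakened. The fallback ANOVA, which tests the group-by-time interaction from T1 to T2, would be affected in the same way.

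**Working it through.** **The plan's own figure.** Sample size calculation gives N = 128 for f = 0.25, power 0.80, alpha 0.05. For two equal groups d = 2f = 0.5. A noncentral F test with 1 numerator df and noncentrality N·f² = 128 × 0.0625 = 8 gives power 0.801 with either no covariate or one, so 128 reproduces (64 per arm). The point here does not alter that calculation.

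**Timing.** From session 1 to session 8 of a weekly programme is 7 weeks. If the first session falls s weeks after randomization, the last falls at week s + 7, and the gap to week 10 is s − 3. The values of s are assumed, since the article gives no waiting time to entry.

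| First session (week) | Last session (week) | Gap to week 10 |
|---|---|---|
| 0 | 7 | 3 weeks early |
| 1 | 8 | 2 weeks early |
| 2 | 9 | 1 week early |
| 3 | 10 | none |
| 4 | 11 | 1 week late |
| 5 | 12 | 2 weeks late |

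Some spread in s is to be expected. Entry opens about every two weeks, the group holds eight, and each block of 20 at 1:1 allocates ten patients to the intervention.

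As a gauge of what a week is worth, the Background cites about 23% spontaneous remission of untreated depression in three months. If linear, that is 23/13 ≈ 1.8 percentage points per week, so a gap of 1 to 3 weeks corresponds to roughly 2 to 5 points. An early intervention T2 gives controls more time to remit and works against the intervention. A late one works in its favour.

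**Missingness: bias.** Let p be the share of the intervention arm without T2, and k the amount, in SD, by which those patients are worse than the ones observed. The full-arm mean is (1 − p) × observed mean + p × missing mean, so a completer-only contrast is biased by p × k, assuming no selective loss among controls. The article gives neither p nor k; all values are assumed.

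| p | k = 0.25 | k = 0.5 | k = 1.0 |
|---|---|---|---|
| 10% | 0.025 | 0.05 | 0.10 |
| 20% | 0.05 | 0.10 | 0.20 |
| 30% | 0.075 | 0.15 | 0.30 |

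At k = 0.5 this is 0.05/0.5 = 10% to 0.15/0.5 = 30% of the planned effect.

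**Missingness: power.** With n₁ = 64(1 − p) and n₂ controls observed, the noncentrality is 0.5/√(1/n₁ + 1/n₂) on n₁ + n₂ − 3 df. With complete controls, power falls from 0.80 to 0.78, 0.75 and 0.72 at p = 10, 20 and 30%. With 10% of controls also missing, it is 0.76, 0.73 and 0.70.

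**The case against.** The strongest reply is that the article is condensed. Posting a form to someone who missed the session is routine conduct that the full protocol may well contain, and the article nowhere says that absentees get nothing. Week 10 is also compatible with eight weekly sessions plus about three weeks for telephone notification, the introductory consultation and the next entry point. Both arguments stand: differential timing and missingness are risks, not stated facts. They do not remove the stated rule itself, which ties T2 to a session in one arm and to the calendar in the other.

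Several stronger readings are tempting, but the article does not support them:

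- *That intervention patients fill in T2 in the therapy room.* Only the handover differs. Stamped return envelopes are provided without distinction of arm, and on-site completion is requested only for the process questionnaires. A different completion setting is not shown.
- *That the procedure as a whole favours the intervention.* That direction applies to selective loss of poor responders and to a late T2. An early T2 works the other way.
- *That imputation would rest on baseline data alone.* Statistical analyses sets no such limit. Documented attendance, session ratings and mailed T3 scores could all be used. Imputation then repairs the loss only if data are missing at random given the variables included.
- *That the whole primary comparison is exposed.* The main outcomes are also compared at T3, which is mailed to both arms.
- *That 0.05 to 0.15 SD is the bias of the planned analysis.* It is a completer-only figure under assumed inputs, whereas the plan is intention-to-treat with probable imputation.

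**Conclusion.** The point holds as a conduct risk. At T2, and only there, delivery of the primary outcome differs by arm, and in the intervention arm it depends on entry date and on attendance at the last session, although T2 is defined as week 10 for all. The session and the calendar agree only for a first session at week 3. With starts anywhere from week 0 to week 5 (assumed), the intervention T2 lies between 3 weeks early and 2 weeks late.

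The effect on the result cannot be sized from the article. The illustrative 0.05 to 0.15 SD rests on 10 to 30% loss, absentees 0.5 SD worse, no selective loss in controls and no imputation. This supports a low-cost improvement to the procedure; it does not establish that the T2 result will be biased.

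**What to change.** Mail the T2 battery to every randomized participant in both arms at 10 weeks after randomization, regardless of attendance, with identical reminders. Hand out only the group evaluation form in the last session. Record the completion date of every T2 form.

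Recruitment was still open in May 2015, so some patients will already have been assessed under the present procedure. For them, report T2 timing and T2 missingness by arm, include attendance and T3 scores in the imputation model, and run a sensitivity analysis on weeks from randomization to completion.

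The cost is at most 64 additional mailings (128/2) and a small procedural amendment. There are two downsides: return among attenders may be slightly lower than with a personal handover, and two delivery procedures will be mixed within the intervention arm, which should be stated in the report. The sample size is unaffected.

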#### Outcome measures

Table 2 shows an overview of all variables and measurements.

**Table 2 Tab2:** Key variables and measurements

Variables	Measurement	T_1_	Monitoring	T_2_	T_3_
Inclusion and exclusion criteria					
Psychiatric disorders (Axis-I)	SCID-I	x	-	-	-
Somatic disorders	self-report in telephone screening	x	-	-	-
Primary outcomes					
Anxiety and depressive symptoms	HADS-D	x	-	x	x
Secondary outcomes					
Psychological distress	BSI	x	-	x	x
Current psychosocial distress	NCCN Distress Thermometer	x	-	x	x
Changes in experience and behavior since baseline	VEV-VW	-	-	x	x
Health-related quality of life	SF-12	x	-	x	x
State of self-esteem	SSES-revised	x	-	x	x
Subjective need for psychotherapy	newly developed questions	x	-	x	x
Process evaluation					
Acceptance of treatment	treatment attendance, self-report	-	x	-	-
Therapeutic processes during the group program from patients’ perspectives	BPSR-G 2000	-	x	-	-
Covariates					
Demographic variables (sex, age, family status, education, employment, and so forth)	demographic survey	x	-	-	-
Psycho-pharmacotherapy	demographic survey	x	-	-	-
Pretreatment of psychiatric disorders	demographic survey	x	-	-	-
Psychological treatment since baseline	self-report	-	-	x	x
Changes in somatic health and psycho-pharmacotherapy since baseline	self-report	-	-	x	x
Coping with a chronic disease	TSK	x	-	-	-

*T*
_*1*_ baseline/pretreatment, *T*
_*2*_ post-treatment/10 weeks after randomization, *T*
_*3*_ follow-up/18 weeks after randomization, *BPSR-G-2000* Bern Post Session Report 2000 modified for groups, *BSI* Brief Symptom Inventory, *HADS*-*D* Hospital Anxiety and Depression Scale, German version, *SCID*-*I* Structured Clinical Interview for DSM-IV Axis I Disorders, *SF*-*12* Short Form Health Survey, *SSES*-*revised* State Self-Esteem Scale, revised version, *TSK* Trier Scales of Coping with Disease, *VEV*-*VW* revised short form of Change Questionnaire of Experience and Behavior

#### Primary outcomes

##### Anxiety and depression

Anxiety and depressive symptoms will be measured with the German version of the Hospital Anxiety and Depression Scale (HADS-D) [41]. The HADS-D has been developed for patients with somatic diseases and assesses two domains: depression and anxiety. Each subscale consists of seven items assessing the severity of anxiety and depressive symptoms within the last week on a scale from 0 to 3. The sum score for every subscale can range from 0 to 21. Subscale scores between 0 and 7 indicate no depression or anxiety, scores between 8 and 10 indicate possible depression or anxiety and scores of 11 or higher indicate clinical depression or anxiety. Both subscales are reliable (HADS-D Anxiety Scale: α = 0.83; HADS-D Depression Scale: α = 0.82) and valid measures of depression and anxiety severity [42].

#### Secondary outcomes

##### Psychological distress

To assess psychological distress we will use the German version of the Brief Symptom Inventory (BSI) [43]. The BSI consists of 53 items and covers nine symptom domains: somatization, obsession-compulsion, interpersonal sensitivity, depression, anxiety, hostility, phobic anxiety, paranoid ideation and psychoticism. Respondents rate their symptom severity within the last seven days on a five-point scale ranging from 0 (not at all) to 4 (extremely). The Global Severity Index (GSI) is the most important of the three global scores and indicates the overall distress level of the respondent. The cutoff point for psychological distress is either a GSI T-score of 63 or higher, or two subscale T-scores of 63 or higher. The BSI is a reliable (α = 0.96 for GSI) and valid measure for the symptom severity of different mental disorders [44].

##### Current psychosocial distress

To assess the current psychosocial distress level we use the first part of the German version of the NCCN Distress Thermometer (DT) [45]. Respondents have to indicate their current distress level within the last week on an 11-point-Likert scale ranging from 0 (no distress) to 10 (extreme distress). Higher scores indicate a higher distress level. The declared cutoff point for psychosocial distress is five or higher. The DT is capable of monitoring changes in psychosocial distress over time [46, 47].

##### Changes in experience and behavior in group psychotherapy or wait-list period

Changes in experience and behavior during the group psychotherapy or wait-list period will be assessed with the Change Questionnaire of Experience and Behavior (VEV-VW) [48], a revised short form of the VEV [49]. The VEV-VW is an instrument for direct measurement of changes in psychotherapy. It consists of 27 items and assesses different situations (common experience, behavior in social situations, experience and behavior in performance situations). The respondent is requested to rate the experienced changes since a given point of time, in our study since the initial consultation. The rating scale ranges from 1 (changes for the better, for example, ‘Now I see the things more optimistically’) to 7 (changes for the worse, for example, ‘Now I see the things less optimistically’). Scores can range from 27 (maximum change for the worse) to 189 (maximum change for the better). Scores above the cutoff point of 108 indicate a better mental wellbeing, and scores below 108 indicate a worse mental wellbeing.

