### Statistical analyses

All analyses will be based on the initial treatment assignment (intention-to-treat). Missing data will be treated according to the recommendations of Hair *et al*. [58]. First, the extent of missing data will be determined; then, the level of randomness (missing at random, missing completely at random or missing not at random) will be diagnosed applying Little’s missing completely at random test and t-tests for independent variables. According to Cho and Leonhart [59], data missing completely at random is very unlikely in a rehabilitation research setting, so missing data will probably be imputed with a missing at random-capable method (for example, using multiple imputations).

We plan to use a between-group analyses of covariance (ANCOVA) with baseline scores of the outcome variables as covariates to adjust for baseline differences. With these, we compare differences in the main outcomes between the intervention and control group at post-treatment (T_2_) and follow-up (T_3_) time points. Alpha levels will be adjusted for multiple testing. Cohen’s *d* will be calculated to measure the effect sizes. All statistical analyses will be performed using IBM SPSS Statistics 20. If we fail to achieve the target sample size within the given time frame and resources of our study, we will use analyses of variance (ANOVA) instead. Due to randomization, group differences at baseline (T_1_) will be not likely. We will then test for an interaction effect between group and time from T_1_ to T_2_ and a main effect of group from T_2_ to T_3_.

Explorative analyses will be conducted to examine potential effect moderators (demographic variables and coping style, such as seeking social integration or seeking information). Interaction terms of potential moderator variables and treatment will be created and analyzed by linear regression.

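### The VEV-VW item anchors contradict the stated direction of its total score, and no recoding step reconciles them

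*Protocol article*

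**What the plan says.** The scoring is described in the protocol article under Secondary outcomes, in the paragraph on changes in experience and behavior.

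- Length: "It consists of 27 items and assesses different situations".
- Low anchor: "The rating scale ranges from 1 (changes for the better, for example, ‘Now I see the things more optimistically".
- High anchor: "to 7 (changes for the worse, for example, ‘Now I see the things less optimistically".
- Total: "Scores can range from 27 (maximum change for the worse) to 189 (maximum change for the better".
- Cutoff: "Scores above the cutoff point of 108 indicate a better mental wellbeing, and scores below 108 indicate a worse mental wellbeing".

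The paragraph gives no rule for getting from item codes to the total.

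On timing, the same paragraph states: "The VEV-VW is an instrument for direct measurement of changes in psychotherapy". Patients rate change since the initial consultation, and Table 2 schedules the scale at T2 and T3 but not at T1.

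The Statistical analyses section plans ANCOVA "with baseline scores of the outcome variables as covariates" and applies it to the main outcomes at T2 and T3. If recruitment falls short, the fallback is ANOVA, with a group-by-time interaction from T1 to T2 and a group main effect from T2 to T3. The study objective lists change in experience and behavior among the outcomes on which the intervention arm is expected to be superior.

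**The concern.** The item anchors put improvement at the low end of the scale, while the total puts it at the high end. Someone who codes the items as described, sums them and reads the sum as described would report improvement as deterioration. This is an outcome with a stated directional hypothesis, so the sign is the result.

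The error would also be hard to see in the data. A reversed total has the same possible range and the same neutral point, so no value would look out of bounds.

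A lesser matter concerns the model. The section describes an ANCOVA on the outcome's own baseline and a fallback that includes a T1-to-T2 interaction. Neither fits a scale that has no T1 value.

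**Working it through.** **Inputs**, all from the VEV-VW paragraph: k = 27 items; item codes 1 (better) to 7 (worse); stated total 27 (maximum worse) to 189 (maximum better); cutoff 108, with higher scores better.

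**Step 1: reproduce the stated figures.** Sum 27 items coded 1 to 7.

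- Minimum: 27 × 1 = 27
- Maximum: 27 × 7 = 189
- Midpoint (every item at 4): 27 × 4 = 108

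All three match the article. The range and cutoff therefore fit a simple sum of 27 seven-point items.

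**Step 2: check the direction.** With the anchors as printed and no recoding:

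- Better on every item: 27 × 1 = 27, labelled maximum change for the worse.
- Worse on every item: 27 × 7 = 189, labelled maximum change for the better.

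The direction is reversed at both ends.

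**Step 3: apply a recoding.** Replace each item x by 8 − x. The recoded total is 27 × 8 − raw sum = 216 − raw sum.

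| Mean item rating (printed anchors) | Raw sum | Article's reading of raw sum | 216 − raw sum | Article's reading of recoded sum |
|---|---|---|---|---|
| 1 (better on every item) | 27 | maximum worse | 189 | maximum better |
| 2 | 54 | worse | 162 | better |
| 3 | 81 | worse | 135 | better |
| 4 (neutral) | 108 | neutral | 108 | neutral |
| 7 (worse on every item) | 189 | maximum better | 27 | maximum worse |

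With recoding, the anchors and the total agree. Swapping the two item anchors in the text, with no recoding, also makes them agree. The range and the midpoint are the same either way, so the stated 27, 108 and 189 cannot show which correction is right.

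**Step 4: effect on the group comparison.** Let m_I and m_C be the arm means of the raw sum. The recoded difference is (216 − m_I) − (216 − m_C) = −(m_I − m_C). Its size is unchanged and its sign flips. For illustration only, suppose the mean item rating is 3 in the intervention arm and 4 in the control arm. The raw difference is 81 − 108 = −27, and the recoded difference is 135 − 108 = +27. The spread is the same under both codings, so Cohen's d changes sign only and a two-sided p-value does not change.

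**Step 5: the missing T1 score.** The scale asks for change since the initial consultation, so a T1 score would have nothing to measure. This leaves the following.

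| Analysis in the Statistical analyses section | Applicable to the VEV-VW? |
|---|---|
| ANCOVA with the outcome's own baseline | No, there is no T1 value |
| Fallback: group-by-time interaction, T1 to T2 | No, there is no T1 value |
| Fallback: group main effect, T2 to T3 | Yes |
| Direct comparison of arms at T2 and at T3 | Yes, though not written out for this scale |

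**The case against.** The article never says that the total is the raw sum of the printed codes. If items are recoded before summing, the anchors and the total are both true, and a condensed article may leave item scoring to the instrument's manual. The meaning of the total is also stated consistently: both the endpoints and the cutoff say that higher is better. A slip in the anchor wording is just as possible. This stands as a limit on the consequence, because reversal is conditional on scoring the items as printed. It does not remove the contradiction. The article gives anchors and a total that disagree unless an unstated step is added, so this is a conflicting statement and not merely a detail left out.

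Three stronger readings are tempting, and the document does not support them.

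- *The result will be reversed.* This follows only if raw codes are summed unreversed and then read by the stated direction. Nothing shows that the trial's syntax does so.
- *Patients will be misclassified at 108.* Under that faulty scoring, every patient not exactly at 108 would fall on the wrong side. However, the Statistical analyses section plans no analysis by this cutoff, which appears only in the description of the instrument.
- *The scale cannot be analysed because it has no baseline.* The blank at T1 is correct for a direct change measure. The arms can be compared at T2 and T3, and randomization makes an unadjusted comparison valid. The sentence applying the ANCOVA names the main outcomes, whereas the VEV-VW is secondary, and its model may be set out in an analysis plan that is not shown.

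**Conclusion.** The contradiction is certain and rests on arithmetic from one paragraph: under plain summation, the printed anchors give the opposite direction to the stated total. What cannot be known from the article is whether a recoding step was left out or the anchors were printed the wrong way round. It is also unknown whether the scoring syntax is affected.

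If raw codes were summed and read as stated, the consequence would be a full change of sign in the group difference on one hypothesised secondary outcome, with no change in its size and nothing in the range of the data to expose it. If the scoring is already right, the defect is confined to the text.

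The absence of a T1 score is not a defect. It means only that the own-baseline ANCOVA and the T1-to-T2 interaction do not carry over to this scale.

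The primary HADS-D analysis and the sample size of 128 are unaffected. The correction should be made because the outcome definition is inconsistent as written and the remedy costs almost nothing.

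**What to change.** 1. Compare the paragraph with the printed questionnaire. If 1 does mean better on the form, add that the total is the sum of (8 − item), that is, 216 minus the raw sum. If 1 means worse on the form, correct the item anchors and leave the total as it stands.
2. Check the scoring syntax against at least one completed form whose answers lie clearly to one side of neutral. A range check is not enough, since both directions give 27 to 189.
3. State that the VEV-VW is compared between arms at T2 and T3 without an own-baseline covariate. Preferably adjust for a T1 measure already collected, such as HADS-D or the BSI Global Severity Index, and name it before the data are analysed. This adjustment is an option to gain precision; validity does not depend on it.

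The cost is one or two sentences of text and at most one line of syntax, with no new data collection. The Trial status section reports recruitment still incomplete in May 2015, so the article leaves room to settle this before the final analysis.
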